#### 3. Multiple Imputation for Missing Compliance Data:

- Missing adherence data will be handled using multiple imputation techniques to minimize bias and maintain analytical power.

Subgroup: We perform subgroup analysis based on EF (LVEF <50, and >50%), gender, age (<65 and ≥65 years), and food insecurity (those with low or very low food security vs. food secure). We will also analyze for significant changes in weight in those with obesity (BMI ≥ 30mg/kg), HbA1c among those with diabetes (HbA1c ≥ 7), and cholesterol (total, triglycerides and LDL) among those with baseline hyperlipidemia.

Semi structured interviews will be audio-recorded and transcribed for thematic analysis. Transcripts will be analyzed using an integrated approach, an iterative process to determine themes and patterns present in the data.[18] The interviewers will develop the initial codebook together, and then will independently dual code subsets of the transcripts to identify common themes and iteratively develop a final codebook, with periodic assessment of inter-rater reliability. We will follow the consolidated criteria for reporting qualitative research (COREQ) guidelines.[19]

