## - Phase II: Comparativeness effectiveness trial of Medically and traditionally tailored meals for Heart Failure

We will conduct a comparativeness effectiveness trial to evaluate the impact of providing medically and culturally tailored Indigenous focused meals delivered to heart failure patients. Meals will be prepared, packaged, and delivered once weekly, with delivery mechanism based on community and patient preference. Two meals will be provided daily for 60 days. Along with the meals, patients will also receive recipe cards with each meal, as well as educational information regarding the meals, traditional food items included, and nutritional information, to educate on the health benefits of the food provided, as well some information regarding the traditional foods included and from where they were sourced. Additionally, patients will receive one cooking class conducted by a Diné Registered Dietician ([name]) to learn how to make a few key recipes from the meal plan, all utilizing locally available ingredients.

**Baseline Characteristics:** In addition to the American Heart Association sociodemographic core measures, we will also collect tribal affiliation, language, and in which local chapter/community patients reside.

**Endpoints:** The primary outcome for the trial will be the proportion of patients who have a hospitalization or ER visit for any cause within 90 days post intervention period (all patients will start the study at t=0 as described above). We will not include hospitalizations that occur electively for an elective procedure.

Secondary outcomes will include: heart failure hospitalizations specifically, ER visits for volume overload specifically (ER visits for lower extremity edema, dyspnea, with clinical evaluation consistent with volume overload), change in weight and body mass index at 60 days from baseline, Kansas City

Cardiomyopathy Score (and its components including summary score, physical limitation score, symptom frequency score, quality of life score and social limitation score)[10], and the following lab parameters and biomarkers at baseline and at 60 days: albumin, prealbumin, creatinine, NT-proBNP, HbA1c, Total cholesterol, LDL-C, HDL-C, Triglycerides, CRP, urine albumin:creatinine ratio. Lab work will be permitted to be collected 14 days before 60 days mark and up to 30 days after (from 46 days-90 days post intervention period).

*Additional secondary outcome measures:*

*Diet Quality*

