#### *General Health Status:*

- We will evaluate patients' general health status using a single general health status question (would you say that in general your health is excellent, very good, good, fair, or poor) at baseline and post-intervention.

Outcomes determined by review of medical, hospital, and billing records, as well as patient surveys and semi-structured interviews. We will also extract medication at baseline and at 60 days to assess for changes in medical therapy. All patients will be provided a scale and blood pressure cuff for weight and blood pressure measurements, respectively. Patients will be instructed to take weights first thing in the morning (or pick a time-up front for all weight measurements for consistency). All patient-reported measures, including KCCQs and CCS-CA scores will be over the phone or in person per patient preference. Patients will come in for lab work at baseline and at 60 days. For patients who are unable to come with for lab work at 60 days (and within the window of 45-90 days), then we will have public health nurses provide outreach to collect blood work in the home. Patients will receive a text message (if they have a cell phone) or phone call on the landline (if no cell phone) to remind them to complete food diaries, weights, and other patient-reported measures in a timely manner. If patients are unable to come in for baseline lab work prior to intervention period, we will use completed lab work as baseline lab work if within 90 days 90 days of the intervention period. For those that have trouble completing written food diaries, we will collect this information verbally over the phone.

For subsequent planning purposes, we will also track costing data to determine the complete cost of the intervention and estimate total program costs (including all resources, even donated, involved in the implementation of the program, but not including research activities such as blood tests).

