## Protection of Human Subjects: Protection of Human Subjects:

This study is aimed at implementing a model to improve access to healthy, nutritious foods for patients. Therefore, this poses a minimal risk to patients. There is prior literature that suggests that medically tailored meal delivery improves quality of life, including Kansas City Cardiomyopathy Questionnaire summary score, as well as potentially a trend to lower heart failure hospitalizations, without significant diet-related adverse events.[4]

However, there are no prior studies of medically and culturally tailored meals in this population. However, our pilot feasibility trial has demonstrated no safety concerns and we will be medically tailoring meals to meet guideline recommendations.[6][7] Meals will be designed with registered dietician input to ensure safety is optimized. Given the short duration of the intervention and low-risk of the intervention, we will not perform interim safety analyses.

Human subjects' involvement, characteristics, and design: The studies outlined in this proposal depend on the enrollment of individuals with heart failure. No vulnerable populations are being specifically

targeted. We are limiting enrollment to individuals above age 18 years as the etiology and practices surrounding heart failure in pediatrics populations differ significantly from those in adults. All data is transmitted in encrypted and secure fashion, stored on servers with "triple-lock" certification, and is available only to members of the study team, IRB, and any state or federal agencies with auditing power.

Sources of Materials: No biological materials will be obtained or stored as part of these studies. Only data, as collected during set time points from the EHR will be obtained. Data includes medical record elements such as demographics, pharmacy records such as medication prescription and dosing, laboratory values, and administrative codes. All data will be stored without PHI. However, we will retain a linking dataset to be able to re-link individual data to actual patients for future studies and ongoing efforts through the HIS. Access to individually identifiable information will be limited to the PI of the study, and only then via a linking file as aforementioned. All data used for analysis and dissemination to other investigators will be de-identified.

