#### **Statistical Considerations**

Sample Size Determination: The primary outcome is the rate of hospitalization or ER visits within 90 days post randomization. Our preliminary data suggests that the hospitalization rate and ER visit for 90 days is approximately 29%, and based on prior data, we hypothesize a reduction to 13% [4]. We will therefore need a sample size of 204 patients to detect a statistically significant difference with 80% power and an alpha error rate of 0.05.

Interim Analysis: Given no safety concerns during our pilot trial, the short duration of the intervention, and low-risk of the intervention, we will not perform interim safety analyses.

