#### Statistical Analysis:

The primary analysis will use the intention-to-treat principle. Between-group differences in baseline characteristics will be assessed using  $\chi^2$  tests for dichotomous variables and 2-sample t tests for continuous variables. Within-group randomization to week 8 changes in continuous outcomes including laboratory evaluation and biomarkers, CCS, and KCCQ score, will be evaluated using paired t-test.

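### The HbA1c analysis in 'those with diabetes' selects patients on HbA1c itself, and the only test named for laboratory changes is a within-group paired t-test, which such selection pushes towards a spurious fall

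*Protocol*

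**What the plan says.** The subgroup paragraph stands at the end of the protocol's statistical section, under the heading on multiple imputation for missing compliance data. After listing the subgroups, it adds a sentence on markers in patients with the matching condition. That sentence begins "We will also analyze for significant changes in weight in those with obesity" and continues with "HbA1c among those with diabetes (HbA1c ≥ 7") and with cholesterol in patients with hyperlipidemia. No other criterion for diabetes appears anywhere in the protocol, and the sentence names no test.

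The Statistical Analysis section supplies the only test for laboratory changes: "Within-group randomization to week 8 changes in continuous outcomes including laboratory evaluation and biomarkers, CCS, and KCCQ score, will be evaluated using paired t-test". The between-group tests named in that section are for baseline characteristics.

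On timing, the Phase II endpoints list HbA1c among "the following lab parameters and biomarkers at baseline and at 60 days", so there is one reading at each time. The paragraph under General Health Status allows an older reading to stand in when a patient cannot attend for baseline blood work: "we will use completed lab work as baseline lab work if within 90 days" of the intervention period.

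On available data, the Sources of Materials paragraph states: "Data includes medical record elements such as demographics, pharmacy records such as medication prescription and dosing, laboratory values, and administrative codes".

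**The concern.** There are two faults.

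First, the label and the rule disagree. A patient with diagnosed, treated diabetes and an HbA1c of 6.8 cannot enter the group, whether the bracket is read as the definition of diabetes or as a further restriction. A result reported for patients with diabetes would describe only those with raised HbA1c.

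Second, patients enter because one reading of the outcome was high. Part of a high reading is chance or passing variation, so the next reading is lower on average with no treatment effect. A paired t-test within an arm attributes that fall to whatever happened in between. In the meal arm it would look like a glycaemic benefit of the meals. Falls of a few tenths of a point could then be reported as a finding.

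**Working it through.** **Check of the plan's own figure.** The subgroup has no stated size, SD or effect, so the only figure that can be reproduced is the primary sample size of 204. The inputs from Statistical Considerations are 29% against 13%, 80% power and alpha 0.05, taken as two-sided. The mean proportion is 0.21.

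n per arm = [1.96 × √(2 × 0.21 × 0.79) + 0.8416 × √(0.29 × 0.71 + 0.13 × 0.87)]² / 0.16² = (1.129 + 0.475)² / 0.0256 ≈ 100.5, so 101 per arm and 202 in total.

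That agrees closely with 204, and 102 per arm gives 80.6% power. Nothing in this point touches that calculation.

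**Size of the spurious fall.** The protocol gives no HbA1c mean, SD or correlation between readings. The following are assumptions for patients with diabetes: mean m from 6.5 to 7.5, SD s from 1.2 to 1.8, correlation r from 0.7 to 0.95, normal distributions, the same mean at both readings, and no meal effect.

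With a = (7 − m)/s and λ = φ(a)/(1 − Φ(a)):

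- mean baseline value of those selected = m + s × λ
- expected fall at the second reading = (1 − r) × s × λ
- share of patients with diabetes left out = Φ(a)

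| m | s | r | a | λ | Share below 7 | Expected fall |
|---|---|---|---|---|---|---|
| 7.5 | 1.2 | 0.95 | −0.417 | 0.553 | 34% | 0.05 × 1.2 × 0.553 = 0.03 |
| 7.0 | 1.2 | 0.90 | 0 | 0.798 | 50% | 0.10 × 1.2 × 0.798 = 0.10 |
| 7.0 | 1.2 | 0.80 | 0 | 0.798 | 50% | 0.20 × 1.2 × 0.798 = 0.19 |
| 6.5 | 1.2 | 0.80 | 0.417 | 1.081 | 66% | 0.20 × 1.2 × 1.081 = 0.26 |
| 6.5 | 1.8 | 0.70 | 0.278 | 0.983 | 61% | 0.30 × 1.8 × 0.983 = 0.53 |

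The first and last rows are the ends of the assumed ranges: about 0.03 to 0.5 points. The cut leaves out 34% to 66% of patients with diabetes.

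**Effect on the tests.** I simulated 4,000 trials per setting with no meal effect, over a narrower set of assumptions (mean 6.5 to 7.5, SD 1.2 to 1.6, correlation 0.80 to 0.95). The subgroup sizes are also assumed. The table gives the share of trials in which the within-arm paired t-test is significant at a nominal 5%.

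| Subgroup patients per arm | Paired t-test within one arm |
|---|---|
| 20 | 6% to 34% |
| 40 | 8% to 59% |
| 60 | 9% to 77% |

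The low ends belong to a correlation of 0.95 and the high ends to 0.80. In the same simulated data, a comparison of mean change between arms was significant in 4.6% to 5.8% of trials, which is the nominal level within simulation error.

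**Baseline window.** Accepting earlier blood work as baseline lengthens the interval between readings for some patients. That would tend to lower the correlation and enlarge the fall, but the protocol gives nothing from which to put a figure on it.

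**The case against.** The strongest reply is that a cut on a baseline value does not bias a randomised comparison. Regression to the mean lowers HbA1c equally in both arms in expectation, and the simulated between-arm test keeps its 5%. That is correct, and it sets the limit of this point. A reader might infer that the subgroup's estimate of the meal effect is biased; the protocol does not support that. The spurious fall misleads only a within-arm reading. The subgroup sentence itself names no test, so the point depends on the paired t-test from the Statistical Analysis section being carried over. A statistical analysis plan, not shown here, may specify a between-arm test. What remains is that the protocol names the within-arm test for laboratory changes and no other.

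A reader might also infer that a day-60 value could place patients in the group, since the hyperlipidemia clause specifies baseline and the diabetes clause does not. That is speculative. For a change from baseline, the baseline value is the only practical reading, and nothing in the protocol suggests membership set after randomisation.

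Restricting a glycaemic analysis to patients with raised HbA1c is ordinary enrichment and may be what was intended. That defends the cut but not the label.

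The size rests wholly on assumed figures and could be negligible if readings correlate at about 0.95. The unit given for the BMI cut-off in the same sentence is a clerical slip with no effect on the analysis.

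**Conclusion.** The point holds in a limited form. The group called patients with diabetes is defined by the outcome marker, so it omits controlled diabetes. The only test named for laboratory changes would also tend to show a fall in that group without any meal effect. The fall is roughly 0.03 to 0.5 points under the assumptions shown, at the low end if the correlation between readings is near 0.95. The comparison between arms is not biased. This is one secondary subgroup analysis and has no bearing on the primary outcome or the sample size. It should be corrected because the change is nearly free, and because choosing between the two group definitions after the data are seen would be a post hoc choice.

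**What to change.** 1. Analyse HbA1c in this subgroup as meals versus usual care, adjusted for baseline HbA1c, and not by paired tests within each arm.
2. Define the diabetes subgroup by a diabetes diagnosis recorded before randomisation, whatever the HbA1c. The Sources of Materials paragraph lists administrative codes; that these include diabetes codes is an inference, though the trial already identifies heart failure by ICD code.
3. Do not use glucose-lowering prescriptions as a criterion. The Exploratory Outcomes section lists SGLT2 inhibitors as heart failure therapy for both reduced and preserved ejection fraction, so a prescription rule would admit patients without diabetes.
4. If the cut at 7 is kept, call the group baseline HbA1c of 7 or more, not diabetes. It can be reported as a second group within the diagnosis-based one.
5. Correct the BMI unit to kg/m² in the same edit.

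The cost is a change of wording, with no new measurements if the diagnosis codes are in the extract. The small downside is that a diagnosis-based group includes patients with less room to improve.
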